#### Losses to follow-up

At enrolment, all patients will be informed of the importance of attending follow-up according to the trial protocol. The principal investigator will endeavour to contact any patients missing a follow-up appointment.

#### Drop-out criteria

Participants will be considered to have left the study if, despite all efforts of the trial team, no reliable determination can be made regarding the primary outcome.

### Schedule

#### Referral

Once referred for ulcer management, patients will be seen within 6 weeks, with the aim of keeping all waiting periods under 1 month.

#### First clinic visit

At their 1st visit to the clinic, patients will be screened, and if found to be eligible, the principal investigator or another designated trial investigator will discuss enrolment. If willing, patients will have their baseline data and wound assessment recorded as above and be randomised and treated on the same day as screening unless they wish to defer enrolment.

#### Deferred enrolment

Patients wishing to take time to think about enrolment will be offered the chance and brought back to the clinic at an interval agreeable to them.

Patients already attending the ulcer clinic will be eligible for enrolment if they present with a new contralateral ulcer.

#### Subsequent follow-up

Patients will attend monthly follow-up, with instructions to the PHN changing their dressings to continue compression until follow-up in all cases. At follow-up appointments, patients will fill a VCSS questionnaire, and the trial nurse will assess their wound and document the BWAT score. Non-healed ulcers will be placed in compression with any other dressings or adjuncts as appropriate and continue follow-up.

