#### Implementation

On enrolment the principal investigator will assign a trial number to the patient and be informed of the ulcer’s size. An envelope will then be taken from the appropriate stratum. The trial number will be written on the envelope, and the envelope passed to the surgical team. The team performing the procedure will sign the envelope sealed, and open it in the operating room immediately before the procedure. A member of the surgical team will then take appropriate consent from the patient for the specific procedure being carried out.

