#### Secondary outcomes

The following are the secondary outcomes:Time to ulcer healing, in those ulcers where complete healing is achievedAbsolute reduction in ulcer sizeRelative reduction in ulcer size as a percentage of original ulcer areaWound regeneration as indicated by changes in Bates-Jensen Wound Assessment Tool (BWAT) score over timeChange in Venous Clinical Severity Score (VCSS) monthly from randomisation to exit from the studyChanges in Charing Cross Venous Ulcer Quesionnaire (CCVUQ) score from randomisation to exit from the study

The BWAT is a tool originally derived for assessing pressure ulcers [26], which has been validated for venous ulcer use [27].

The VCSS is an objective measure of the severity of venous disease, encompassing both ulceration and wound factors, as well as non-wound related signs and symptoms [28].

The CCVUQ is a quality of life questionnaire specific to venous leg ulcers [29].

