### Method of blinding

The trial will be assessor blinded. The trial nurse(s) will assess all wounds prior to randomisation and will be blinded to treatment allocation throughout, performing assessments at each follow-up visit. Patients will be instructed not to reveal the nature of their treatment in follow-up. The operation note from the intervention will be filed in the patient notes to allow intentional or emergency access. All members of the trial team involved in data collection and analysis will not be present when the envelope is opened at the time of treatment.

Any treatment decisions required beyond the trial protocol will be made by a member of the surgical team who is already unblinded.

Ultrasound assessment of treated veins will be avoided unless otherwise indicated, to minimise risk of inadvertent unblinding of assessors.

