#### Ulcer characteristics

Along with the above baseline characteristics, the following data related to the wound itself will be documented:Ulcer locationUlcer durationUlcer area (in cm^2^)Depth (in terms of tissue layers involved)Condition of wound edgesUnderminingNecrotic tissue typeNecrotic tissue amount (as a percentage of wound area)Exudate typeExudate amountSurrounding skin colourSurrounding tissue oedemaSurrounding tissue indurationGranulation (as a percentage of wound area)Epithelialisation (as a percentage of wound area)Pain (present or not, and relieved by medications or not)

At follow-up visits only:17.Compliance with compression

These data will be recorded by the trial nurse and a BWAT score and VCSS will be calculated.

At each review appointment, the same data will be collected, and progress of the wound assessed using the BWAT. VCSS will also be monitored monthly.

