#### Final follow-up

Once a patient has attended for follow-up and their ulcer has healed, they will exit the trial. If the ulcer does not heal by 24 weeks post-intervention, these patients will exit the trial at this point. At their final visit, patients will have a BWAT score, VCSS and CCVUQ questionnaire recorded. All patients completing follow-up, either through completion of 6 months or having healed their ulcer, will be seen by a member of the clinical team in the ulcer clinic who will determine ongoing follow-up management.

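### The protocol gives two incompatible accounts of who scores the VCSS at follow-up: one ties it to the blinded nurse's record, the other has the unblinded patient fill it in

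*Protocol article*

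**What the plan says.** The protocol article lists monthly change in VCSS, from randomisation until the patient leaves the study, among its secondary outcomes. It describes the score this way: "The VCSS is an objective measure of the severity of venous disease". Four places bear on who produces it.

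- **Data collection, Ulcer characteristics:** "These data will be recorded by the trial nurse and a BWAT score and VCSS will be calculated". The section goes on to say that the same items are gathered at every review, and then: "VCSS will also be monitored monthly".
- **Schedule, Subsequent follow-up:** "patients will fill a VCSS questionnaire, and the trial nurse will assess their wound and document the BWAT score".
- **Schedule, Final follow-up:** "At their final visit, patients will have a BWAT score, VCSS and CCVUQ questionnaire recorded".
- **Method of blinding:** "The trial nurse(s) will assess all wounds prior to randomisation and will be blinded to treatment allocation throughout, performing assessments at each follow-up visit".

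Patients are not blinded. Under Implementation, once the envelope has been opened, a member of the surgical team will "take appropriate consent from the patient for the specific procedure being carried out". Method of blinding adds: "Patients will be instructed not to reveal the nature of their treatment in follow-up".

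**The concern.** The Subsequent follow-up sentence divides the work at each visit: the VCSS goes to the patient, and the wound and BWAT go to the nurse. Ulcer characteristics does not divide it that way. There both scores come from the nurse's record.

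The difference matters because the trial's protection against biased assessment rests on the nurse not knowing the allocation, and the patient does know it. A patient who expects more from a catheter procedure than from an injection, or the reverse, could score accordingly, and that would enter the between-arm comparison of VCSS. A reader of the results would also be told that the score is objective in an assessor-blinded trial, when it might be neither.

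**Working it through.** No arithmetic in the plan bears on this point, so the check is a comparison of the text.

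**Step 1. Who scores the VCSS at each visit, by section?**

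| Section | Baseline | Monthly visits | Exit visit |
|---|---|---|---|
| Ulcer characteristics | from the nurse's record | same data at each review, no change of rater announced | not separately stated |
| Subsequent follow-up | not covered | patient | not covered |
| Final follow-up | not covered | not covered | rater not named |

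The two sections that cover the monthly visits disagree. The only section that describes the exit visit is in the passive voice and cannot break the tie. Ulcer characteristics also uses the passive for the calculation itself, so nurse scoring is its natural reading but is not stated outright.

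**Step 2. Which reading fits the rest of the protocol?** Three places favour the nurse.

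- The Secondary objective section lists objective venous disease severity separately from patient-assessed quality of life.
- The Secondary outcomes section says that the VCSS covers ulceration and wound factors as well as other signs and symptoms. The nurse assesses the wound at the same visit.
- The Quality of life data section names only the CCVUQ as an instrument that participants complete.

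These make nurse scoring the likelier intention. None of them withdraws the sentence in the schedule, which is the section that staff would follow on the day.

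**Step 3. Does the patient know the allocation?** Yes. Consent to the specific procedure follows the opening of the envelope, and the instruction not to disclose the treatment presumes that the patient knows it.

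**Step 4. What follows if the patient scores at follow-up?** Write the follow-up score as the true value, plus an offset *r* for patient rather than nurse scoring, plus a shift *b* that depends on the treatment the patient knows was given. The baseline comes from the nurse before allocation. Then:

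- mean change within an arm = true change + *r* + *b*(arm);
- difference between arms in mean change = true difference + [*b*(TIRS) − *b*(AA)].

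If *r* is the same in both arms, it drops out of the difference. It distorts the reported change from baseline but does not by itself bias the comparison. The between-arm risk is the bracketed term, which arises from unblinded self-scoring.

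**Step 5. How large could that term be?** The protocol gives no VCSS standard deviation and nothing from which to estimate *b*. Any error rate would reflect invented inputs, so none is offered.

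**The case against.** The best defence is that nurse scoring is what the protocol means and the schedule sentence is loose drafting. Ulcer characteristics covers follow-up as well as baseline, and the Personnel and Method of blinding sections both place the blinded nurse at every follow-up visit. On that reading the blinding of the VCSS is intact. This is plausible, and it is why the point is conditional. It does not remove the conflict, since the schedule names the patient in plain terms.

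A second defence is that the blinding was only ever claimed for wounds. The abstract speaks of assessors reviewing wounds, and Method of blinding refers to wound assessment. The CCVUQ is also patient-completed and unblinded, and rightly draws no criticism. This has some force: the protocol never says in terms that the VCSS is blinded. But the CCVUQ is presented as patient-assessed, whereas the VCSS is presented as objective. That description does not fit unblinded self-scoring.

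A third point stands in full. The score includes symptoms, so some input from an unblinded patient remains even when the nurse scores it. Nurse scoring reduces the risk but does not abolish it.

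A reader might infer more: that the VCSS has lost its blinding and that the change of rater biases the treatment comparison. The documents do not support this. The loss of blinding follows only if the schedule sentence governs, and a change of rater common to both arms cancels in the comparison, as shown in the working.

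**Conclusion.** The inconsistency is established on the text: the protocol gives two accounts of who scores the VCSS at monthly follow-up and none for the exit visit. The consequence is conditional. If patients score it, post-treatment VCSS is unblinded, does not match its description as objective, and is open to between-arm bias of unknown size and direction. Within-patient change is then also blurred, to the same degree in both arms if the rater offset does not depend on treatment. If the nurse scores it, only the wording needs repair.

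The reach is limited to one of six secondary outcomes. The primary outcome and the BWAT rest on the blinded nurse's wound assessment under either reading. The point is worth correcting because the remedy is nearly free, but it does not threaten the trial's main conclusion.

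**What to change.** Reconcile Ulcer characteristics, Subsequent follow-up and Final follow-up so that all three name the same rater. The preferable version is that the blinded trial nurse scores the VCSS on the same form at baseline, at each monthly visit and at exit, asking the patient about symptoms where an item requires it.

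If patients do complete the score at follow-up and this is to continue, have them also complete it at baseline, so that change is measured by one rater. Then describe and report the VCSS as an unblinded patient-reported outcome and drop the word objective from the objectives and the outcome description.

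The Trial status section says that enrolment is ongoing, so some scores will already exist. State in the report who produced them.

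The cost of the preferred version is a sentence in each section and a rater field on the case report form. It needs no extra visit, since the nurse already assesses patients at each one. The alternative adds one form at baseline.

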#### Final follow-up

Once a patient has attended for follow-up and their ulcer has healed, they will exit the trial. If the ulcer does not heal by 24 weeks post-intervention, these patients will exit the trial at this point. At their final visit, patients will have a BWAT score, VCSS and CCVUQ questionnaire recorded. All patients completing follow-up, either through completion of 6 months or having healed their ulcer, will be seen by a member of the clinical team in the ulcer clinic who will determine ongoing follow-up management.

### Dissemination

#### Registration

The trial is registered at ClinicalTrials.gov, reference number NCT04484168.

#### Reporting

The trial protocol will be published in a suitable peer-reviewed journal and recorded in keeping with the SPIRIT guidelines [30]. Trial results will be submitted for peer-reviewed publication regardless of outcome. The principal investigator will have the responsibility for drafting the manuscript, and all co-authors will have editorial input.

## Discussion

TIRS has not yet been tested in a randomised trial, so this will be the first rigorous test of the efficacy of TIRS. By comparing TIRS against AA, there is the opportunity for significant savings in healthcare resources because TIRS using sclerosant foam is less expensive and less time consuming than AA, as well as less invasive. If the results of TIRS are comparable to those of AA, then a significant savings resources could be made.

The EVRA trial required that all participants undergo treatment to the lowest point of reflux but did not specify that all participants undergo formal ablation, and patients may have been treated with foam from the lowest point of reflux, in a manner similar to the aim of TIRS. The results of this trial will help to refine best practice in how reflux ablation to aid in ulcer healing is delivered in practice. The results of this trial may also serve to support the findings of EVRA if similar high healing rates are seen with either or both forms of ablation.

## Trial status

Protocol version 3

AAVTIRS began recruiting on 21 July 2020 and was registered on 23 July 2020.

Enrolment is ongoing. Projected completion of enrolment is in the first half of 2022, with completion is projected in late 2022 follow-up after the final participants have completed 6 months of follow-up.

## Data Availability

The datasets during and/or analysed during the current study are available from the corresponding author on reasonable request.

## Abbreviations

AA: Axial Ablation
TIRS: Terminal interruption of the reflux source
BWAT: Bates-Jensen Wound Assessment Tool
CCVUQ: Charing Cross Venous Ulcer Questionnaire
VCSS: Venous Clinical Severity Score
MOCA: Mechanical Occlusion with Chemical Assistance
CRF: Case report form
BMI: Body mass index
ABI: Ankle Brachial Index
UHG: University Hospital Galway
PHN: Public Health Nurse
